### Data collection and measurement

#### Data collection

Data will be collected at each identified time point and during the eligibility screening process. A research study assistant, blinded to the study objectives and randomization, administers the screening questionnaire verbally. Baseline and T_1_ data collection will be completed during an in-person meeting where they complete questionnaires via computer and provide a blood sample. Saliva will be collected over 2 days at home in close proximity to these data collection points. Participants can complete T_2_ questionnaires remotely by computer. Following study completion, we will conduct a medical record review. Finally, a subset of GET-assigned participants (*n* = 6) will be asked to participate in a qualitative exit interview to gather subjective experiences of participation. See Table 2 for the data collection plan.

**Table 2 Tab2:** Data collection scheme

	Enrollment	Assessment					Close-out
Timepoint	Pre T_0_	T_0_	Post baseline	T_1_	T_2_	Post T_2_	Chart review
Screening							
Eligibility screen	X						
Informed consent	X						
Allocation			X				
Interventions							
GET							
ISP							
Assessments							
Hospital Anxiety and Depression Scale (HADS)		X		X	X		
Goal Navigation (CAYA-T)		X		X	X		
Emotion Regulation Questionnaire (ERQ)		X		X	X		
Career Thoughts Inventory (CTI)		X		X	X		
Blood draw		X		X			
At-home saliva sampling		X		X			
Demographics		X					
Semi-structured interview						X	
Medical chart review							X

*CAYAQ-T* Cancer Assessment for Young Adults—Testicular, *GET* Goal-Focused Emotion-Regulation Therapy, *ISP* Individual Supportive Psychotherapy, *T*_*0*_ baseline, *T*_*1*_ post Intervention, *T*_*2*_ 12-week follow-up

#### Measures

##### Screening measures

Two measures are used in participant screening, as described earlier: the Distress Thermometer (DT) and the Cancer Assessment for Young Adults (CAYA-T; Goal Navigation Skill subscale). The DT [39] is a single-item visual analog scale used to screen cancer patients and ICs for psychological distress with a 0–10 range accompanied by a 34-item problem checklist [49]. Extensive research has identified a score of 4 or greater for identifying clinically significant distress [50, 51].

Goal navigation skill is measured by the goal navigation scale of the CAYA-T [28]. The CAYA-T has been validated on a sample of young adult men with testicular cancer and has demonstrated good psychometric properties in this population.

##### Depression and anxiety symptoms

Depression and anxiety will be assessed using the Hospital Anxiety and Depression Scale (HADS) [52], a 14-item self-rated questionnaire of overall psychological distress, well tested in cancer populations [53].

##### Emotion regulation

Emotion regulation skills will be measured by the Emotion Regulation Questionnaire (ERQ) [54]. The ERQ is a widely used 10-item scale designed to measure respondents’ tendency to regulate their emotions in two ways: cognitive reappraisal and expressive suppression. Respondents answer each item on a 7-point scale ranging from 1 (strongly disagree) to 7 (strongly agree).

##### Goal navigation

Goal navigation skill is measured by the goal navigation scale of the CAYA-T, as already described. In addition, goal regulation capacity will be measured by agency and pathways. The Hope Scale [55] is a 12-item measure of a respondent’s level of hope. In particular, the scale is divided into two subscales that comprise Snyder’s cognitive model of hope: agency (i.e., goal-directed energy) and pathways (i.e., planning to accomplish goals).

##### Career confusion

Career confusion will be measured with the Career Thoughts Inventory (CTI) [56]. The CTI is a 48-item measure that is designed to assess career navigation difficulty and is normed on adult populations. The CTI yields a total score as well as scores on three construct scales: decision-making confusion, commitment anxiety, and external conflict.

##### Demographic and clinical information

Demographic information, past/current psychosocial service use, support needs, intervention preferences, and perceived barriers are assessed through Likert-scale ratings and open-ended items. Clinical information will also be assessed via medical record review and via self-report. In addition, we will thoroughly assess for medical comorbidities and physical health symptoms.

#### Biological assessments

##### Inflammatory markers

We will focus on five inflammatory biomarkers that have proinflammatory function, are associated with distress symptoms, and/or have angiogenic properties: IL-6, IL-1RA, CRP, sTNFrR2, and VEGF. Blood samples for circulating inflammatory markers will be collected between the hours of 8 a.m. and 4 p.m. by a trained phlebotomist by venipuncture into EDTA heparinized tubes, placed on ice, centrifuged for acquisition of plasma within 30 min, and stored at − 80 °C for subsequent batch testing. Plasma levels of identified markers will be determined by enzyme-linked immunosorbent assay according to the assay manufacturer’s protocols. CRP will be determined by a high-sensitivity enzyme-linked immunosorbent assay according to the assay manufacturer’s protocol. All samples will be run in duplicate, and assays will be repeated on two separate days for sTNFr and IL-6; intraassay and interassay mean levels will be used in all analyses.

##### Diurnal salivary stress biomarkers

We will focus on two salivary stress biomarkers. These include *s*alivary cortisol, as a downstream marker of HPA activity, and salivary α-amylase (sAA), as a proxy measure of SAM activation; they can be measured concomitantly [57] and together offer a comprehensive view of physiological stress, as differing diagnostic and treatment effects have been observed between these markers [58]. Both salivary cortisol and sAA follow a distinct diurnal rhythm: cortisol levels peak approximately 30 min after awakening and decrease throughout the day, whereas sAA has a pronounced decline after awakening followed by an increase across the day [57].

Diurnal rhythm in salivary markers will be measured over 2 days at baseline and post intervention. Participants will collect saliva samples in their natural environment upon awakening, 30 min later, 8 h later, and at bedtime as recommended by Nicolson [38]. Participants will be instructed to go about their normal daily activities on the days of data collection and will complete a diary to assess relevant health behaviors (e.g., caffeine use). To avoid sample contamination, they will be instructed to avoid brushing their teeth, eating, or drinking within 20 min before sampling. Participants will be instructed to keep samples refrigerated prior to returning them to the research laboratory and returned salivettes will be stored in a freezer at – 80 °C until analyzed. After data collection is complete, salivary markers will be analyzed with a time-resolved fluorescence immunoassay. Several indices will be computed including diurnal slope, area under the daily curve, cortisol awakening response, and total daily cortisol output.

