### Hypotheses

We hypothesize that young adult testicular cancer survivors will confirm the formative findings that the GET intervention is feasible, tolerable, and acceptable. Furthermore, we expect that, in comparison to those in Individual Supportive Therapy (ISP), participants receiving GET will have a measurable, positive improvement on potential primary and secondary outcomes. Primary outcomes of consideration are change in psychological distress (i.e., depressive and anxiety symptoms) from baseline to 12 weeks post intervention and change in systemic inflammation markers (i.e., IL-6, IL-1ra, CRP, sTNFαRII) and salivary cortisol regulation (i.e., diurnal cortisol slope and daily cortisol output) from baseline to post intervention. However, results related to changes in distress symptoms will inform sample size estimates in future trials. Of additional focus are changes in self-regulatory processes (i.e., emotion regulation and goal navigation skills, career confusion) from baseline to 12 weeks post intervention.

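### The 20-minute abstention rule leaves the first 10 minutes after the awakening saliva sample open to food, coffee or tooth-brushing, which may add noise to the +30 min sample

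*Protocol article*

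**What the plan says.** All of the collection rules are in the protocol article under Diurnal salivary stress biomarkers.

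- **Schedule:** "Participants will collect saliva samples in their natural environment upon awakening, 30 min later, 8 h later, and at bedtime". This is repeated on more than one day: "Diurnal rhythm in salivary markers will be measured over 2 days at baseline and post intervention".
- **Abstention rule:** "they will be instructed to avoid brushing their teeth, eating, or drinking within 20 min before sampling". Its stated purpose is to avoid contaminating the sample. It is given once, for all samples, with no separate instruction for the interval between the first two.
- **Behaviour on sampling days:** men keep to their usual routine and fill in a diary of health behaviours, with caffeine as the example. The article does not say whether the diary records times, or how the entries will be used.
- **Physiology:** "cortisol levels peak approximately 30 min after awakening and decrease throughout the day". Salivary α-amylase is said to fall markedly after awakening and then rise.
- **Indices:** slope, area under the daily curve, awakening response and total daily output are all to be computed. No formulas are given. The Hypotheses section puts "salivary cortisol regulation (i.e., diurnal cortisol slope and daily cortisol output) from baseline to post intervention" among the primary outcomes of consideration; the awakening response is not named there.

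**The concern.** The protocol treats eating, drinking and tooth-brushing as sources of contamination and caffeine as a behaviour worth recording. Yet its single rule is shorter than the gap between the first two samples. The uncovered minutes fall where, on the article's own account, cortisol is rising to its peak and α-amylase is falling fast. A man who keeps to his usual morning may have coffee directly after the awakening sample and still comply.

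What is at stake is the quality of the +30 min sample. It sets the awakening response jointly with the awakening sample. Because no sample lies between +30 min and 8 h, it also stands for a long stretch of the day in any trapezoid area. If intake in the open window alters the reading, and the morning routine differs between days or between the two assessment points, the change scores become noisier. The Background section makes testing data collection procedures and measurement strategies a major focus of this pilot, so a gap in the instruction could carry over into the larger trial.

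**Working it through.** The plan states no figure to reproduce here. The check is interval arithmetic, followed by the leverage of the +30 min sample under stated assumptions.

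**1. Open window.** The gap between samples is 30 min and the abstention period is 20 min (both from the article). 30 − 20 = 10 min, or 10/30 = 33% of the interval.

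**2. Weight of the +30 min sample in a linear-trapezoid area (assumed formula).** For sampling times t1 to t4, the weight of the second sample is (t3 − t1)/2. With t1 = 0 and t3 = 8 h this is 4.0 h, whatever the bedtime. With bedtime assumed at 16 h, the four weights are 0.25, 4.0, 7.75 and 4.0 h. As a share of total time the weight is 4/18 = 22% to 4/14 = 29% for bedtimes of 18 to 14 h. If the third sample is 8 h after the second, the weight is 4.25 h and the share reaches 4.25/14 = 30%.

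**3. Share of the area.** The documents give no cortisol values, so profiles are assumed relative to awakening = 1: +30 min 1.1 to 1.75, 8 h 0.2 to 0.5, bedtime sample 0.1 to 0.3, bedtime at 14 to 18 h.

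| Assumed profile (0, +30 min, 8 h, bed) | Bedtime | Area | Share of +30 min sample |
|---|---|---|---|
| 1, 1.1, 0.5, 0.3 (lowest) | 18 h | 0.25 + 4.4 + 4.375 + 1.5 = 10.525 | 42% |
| 1, 1.5, 0.35, 0.15 (central) | 16 h | 0.25 + 6 + 2.7125 + 0.6 = 9.5625 | 63% |
| 1, 1.75, 0.2, 0.1 (highest) | 14 h | 0.25 + 7 + 1.35 + 0.3 = 8.9 | 79% |

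The share exceeds 50% in 89% of the grid. A separate illustration in absolute units (12, 18, 4 and 1.5 nmol/L at 0, 0.5, 8 and 16 h) gives 3 + 72 + 31 + 6 = 112 nmol·h/L, of which 72 (64%) comes from the +30 min sample.

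**4. What an error in that sample would do.** A proportional error e moves the area by e × share. An assumed 10% error therefore moves it by 4.2% to 7.9% across the grid, and by 6.3% in the central profile. The awakening response, taken as the rise from 0 to +30 min, moves by e × p/(p − 1), where p is the +30 min value relative to awakening. For p = 1.5 that is 3e, or 30% for a 10% error.

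**5. Slope.** In the absolute-unit illustration, a least-squares slope through all four points goes from −0.90 to −0.96 nmol/L per h when the +30 min value is raised by 10%. A slope through the other three points is −0.66 and does not move. Whether the slope is affected therefore depends on a formula that the article does not give.

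**The case against.** The strongest reply is that the causal step is not in the documents. The article presents 20 min of abstention as the measure that avoids contamination. By that standard, a man who ate at minute 5 gives a clean sample at minute 30, and nothing shown says otherwise. This stands against any claim that the sample is contaminated. It does not remove the gap: caffeine is recorded as a relevant behaviour, and one rule serves both the steepest part of the curve and the rest of the day.

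A second reply is that an article condenses participant instructions. The Discussion mentions a demonstration video and smartphone applications that record timing and compliance, and the schedule follows a cited recommendation. Fuller wording may exist. However, the rule printed is a specific figure rather than an omission, and as printed it leaves the window open.

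Third, a man with the same morning routine on every sampling day carries much the same error at both assessments, and it would largely cancel in his change score. That is fair, and it limits the harm to men whose routine varies.

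Several stronger readings are tempting and are not supported:

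- **Most of daily output rests on one exposed sample.** This needs an assumed profile and a trapezoid formula, and the grid runs from below to well above one half.
- **Both cortisol outcomes in the Hypotheses are affected.** Slope is affected only if it uses the +30 min point. The most sensitive index, the awakening response, is not among those outcomes.
- **The arms would be biased differently.** The only hook is that GET session 5 (Table 1) includes self-care behaviour, which says nothing about breakfast or coffee. Both arms follow the same rule.
- **The slope and area should be redefined.** Those derivations may sit in an analysis plan that is not shown, and they are analyst choices whatever the food rule.

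**Conclusion.** The point holds as a small, cheap improvement to the collection instruction. It is certain that the printed rule leaves 10 of the 30 min uncovered. It is uncertain how much this matters, because the documents give no effect of intake 20 to 30 min before a sample. The 10% error used above is an assumption that shows leverage and does not estimate harm.

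The likely consequence is added noise in the awakening response and in any trapezoid area, where the +30 min sample carries about 42% to 79% under the assumed profiles. Bias between arms would require intake in the window to change differently by arm after treatment; this is possible but not shown. No sample size, power or error-rate figure changes. The Discussion treats observations of change as preliminary, and the Hypotheses section ties future sample size to distress symptoms. The case for acting therefore rests on clean measurement in a pilot meant to test it.

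**What to change.** Change three lines in the participant instructions, the demonstration video and the diary:

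1. From waking until the +30 min sample has been taken, have nothing but water and do not brush teeth. Read literally, the present rule also bars water in the last 20 min. The new line should say whether that still applies; if it does, nothing in the present rule is relaxed.
2. Keep the 20-min rule for the 8 h and bedtime samples.
3. Have the diary record the time of any intake in the first 30 min after waking, so that departures can be identified.

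Apply the new wording to newly enrolled men only, so that no participant has different rules at T0 and T1. Recruitment began in January 2017 and was expected to complete by October 2020, so two sets of men would exist. With 1:1 allocation in blocks of 10, the arms should be nearly balanced on either side of the switch. The version of the instruction should be recorded for each man.

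The cost is breakfast or coffee delayed by up to 30 min on four days (2 days at each of two assessments). The definitions of slope and area need no change on this account.

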#### Evaluation data

##### Qualitative interview

Six participants who complete the GET sessions will be invited to complete a semi-structured qualitative interview, using a semi-structured interview guide. Consecutive participants completing GET will be offered participation in the interviews until six interviews are completed. The interview will focus on understanding feasibility, tolerability, and acceptability of GET and overall trial participation from the patient’s perspective. Through the interviews, participants will provide information about their experience of participating in GET, including challenges to their participation and elements that they found most and least appealing. Qualitative methods will be employed to elicit and evaluate participant responses to the semi-structured interview. The interview transcripts will be analyzed with a targeted inductive procedure of qualitative thematic text analysis [59]. This process will involve thorough reading and review of transcripts by an analysis team; synthesizing key conceptual findings of each transcript; identifying key conceptual findings across all transcripts; and generating descriptive and interpretive themes for the entire data set.

##### Patient satisfaction

A 16-item questionnaire administered after the last session was adapted from a measure used in currently/past federally funded intervention studies. Items query subjects’ responses to the various components of the intervention (e.g., content, timing, and length of sessions), and will be used for intervention modification.

#### Descriptive data

We will use descriptive statistics to summarize multiple aspects of study feasibility, including acceptability (percentage of approached and eligible men who consent to the study), tolerability (percentage of consented and enrolled men who complete the study in both arms), and adherence (descriptive statistics summarizing the rate of patients completing the scheduled sessions for both arms).

#### Data analysis

Standard descriptive statistics will be used to report baseline participant characteristics by condition. For continuous variables with markedly non-normal or skewed distributions, appropriate transformations may be required, such as natural logarithms, and will be applied as necessary and appropriate. We will perform analysis according to the intention-to-treat principle (i.e., participants will be analyzed according to the treatment group to which they will be randomly allocated regardless of dropout or treatment adherence status).

Change from baseline will be calculated across variables. Follow-up scores on the identified variables will be compared between study conditions (adjusting for baseline), via repeated-measures analysis of covariance (ANCOVA). We will also reference established cutoff values for clinically meaningful differences for scores on the HADS to identify ranges and patterns of change. Mixed-effects models will be used to model the scores over time for each group. Time since diagnosis, education, marital status, medical comorbidities, and age will be examined as potential covariates to model.

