**Fig. 1 Fig1:**
[figure not shown]
Study schematic. GET Goal-Focused Emotion-Regulation Therapy, ISP Individual Supportive Psychotherapy, R randomization, Sn session number, T_0_ baseline, T_1_ post Intervention, T_2_ 12-week follow-up

The replication and extension of the promising and preliminary results of our formative research (described in the following) will contribute to satisfying the critical need for accessible, feasible, effective, and scalable interventions for young adult survivors with the goal of ameliorating long-term negative effects of cancer and cancer treatment. Participants will be 60 young adults with testicular cancer who have completed treatment (including chemotherapy) and will be randomized 1:1 into GET or ISP using a block of 10 randomization design. A central randomization scheme will be used in which a research recruiter will contact a central methods center by secure computer for allocation assignment for newly enrolled participants to maintain concealment of the randomization sequence. The sequence will be generated by a computer randomization program.

Sample size was determined by balancing realistic recruitment estimates and minimal sample requirements for planned analyses. Informed consent will be obtained individually following eligibility screening and prior to data collection. The interventions will be delivered face to face in a clinical setting. However, to enhance accessibility, telephone sessions will also be possible for those with accessibility barriers.

Participants will complete questionnaire assessments at baseline (T_0_), at the completion of the last GET or ISP session (T_1_), and at 12 weeks following completion of the last GET or ISP session (T_2_). In addition, biological specimens will be collected at T_0_ and at T_1_. These include the collection of plasma via venipuncture (in the clinic) and samples of saliva (at home). Saliva is collected over 2 days at each assessment point upon awakening, 30 min later, 8 h later, and at bedtime [38]. Questionnaire data will be collected via an online password-protected data collection platform. All participants will be offered $50 at each data collection point for completion of assessments and collection of biomarkers (and $25 without biomarker assessment).

All study procedures will be reviewed and approved by the University of California, Irvine and Memorial Sloan Kettering Cancer Center Institutional Review Boards.

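### The between-arm comparison is assigned to repeated-measures ANCOVA, which in its classical form uses completers only and averages T1 with T2, and the planned mixed model is not tied to the T2 contrast hypothesised

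*Protocol article*

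**What the plan says.** Three statements in the Data analysis section bear on this.

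- Intention to treat: "participants will be analyzed according to the treatment group to which they will be randomly allocated regardless of dropout or treatment adherence status".
- The comparison of arms: "Follow-up scores on the identified variables will be compared between study conditions (adjusting for baseline), via repeated-measures analysis of covariance (ANCOVA".
- A second model: "Mixed-effects models will be used to model the scores over time for each group".

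The Hypotheses section fixes the time points. For distress the outcome is "change in psychological distress (i.e., depressive and anxiety symptoms) from baseline to 12 weeks post intervention", and the self-regulation outcomes are likewise set "from baseline to 12 weeks post intervention". That visit is T2. The biomarker hypotheses concern change to post intervention.

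Questionnaires are collected at T0, T1 and T2 (Table 2), so they have two follow-ups. Biomarkers have one: T1 in Study design and Table 2, although the Abstract says T2.

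The Hypotheses section adds that the distress results will inform sample size in future trials. The Discussion says that observed changes will be treated as preliminary.

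**The concern.** Only one sentence assigns a method to the comparison of arms, and that method sits badly with two other commitments.

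First, classical repeated-measures ANCOVA, with T1 and T2 as the repeated outcomes and baseline as covariate, needs both follow-up scores from each man. Anyone missing one drops out of the comparison. If loss is related to distress, and differently so in the two arms, the remaining men are no longer a fair randomised comparison.

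Second, the arm effect that this model reports by default is the mean of the T1 and T2 differences. The hypothesis is about T2. The arm-by-time test does not fill the gap either, because it tests whether the T2 difference departs from the T1 difference. A T2 contrast has to be requested, and the section does not request one.

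The mixed-effects model could meet both commitments, but its sentence does not link it to the comparison of arms or to T2. At stake is the distress estimate that is meant to carry forward into planning the next trial.

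**Working it through.** The protocol gives no power, alpha, effect size, SD or dropout rate, so there is no figure of its own to reproduce. Its only inputs here are the total ("Participants will be 60 young adults with testicular cancer who have completed treatment") and the allocation ("will be randomized 1:1 into GET or ISP using a block of 10 randomization design"), which give 30 per arm. On the size of the trial it says: "Sample size was determined by balancing realistic recruitment estimates and minimal sample requirements for planned analyses". Everything else below is assumed.

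**Step 1. How many men a completers-only analysis keeps.** Completers = 60 × (1 − dropout). At 10%, 20% and 30% this is 54, 48 and 42. Take a T2 effect of 0.5 SD, a baseline–outcome correlation of 0.5 (adjusted SD = √(1 − 0.25) = √0.75) and two-sided alpha of 0.05. Power is then 0.61 with no loss and 0.56, 0.52 and 0.46 at those dropout rates.

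**Step 2. Which effect each term targets.** Let d1 and d2 be the arm differences at T1 and T2. The arm main effect targets (d1 + d2)/2, the arm-by-time term targets d2 − d1, and the T2 contrast combines the two to give d2.

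| d1, d2 (SD) | Main effect | Arm-by-time | T2 contrast |
|---|---|---|---|
| 0.5, 0.5 | 0.50 | 0 | 0.5 |
| 0.2, 0.5 | 0.35 | 0.3 | 0.5 |
| 0, 0.5 | 0.25 | 0.5 | 0.5 |
| 0.5, 0.2 | 0.35 | −0.3 | 0.2 |

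With equal effects nothing is lost. With a growing effect the average understates T2, and with a fading effect it overstates T2.

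**Step 3. Bias from using completers only.** Two sets of simulations had a true T2 effect of 0.50 SD favouring GET and loss at T2 driven by the T1 score. Each compared completers-only ANCOVA at T2 with a likelihood estimate. The likelihood estimate is the arm coefficient for T2 given baseline and T1 among completers, plus the T1 coefficient times the arm effect on T1 in all men.

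- Set A: all correlations 0.5, 400,000 simulated men, loss of about 18% to 25%. Completers-only gave 0.50 when loss was random and about 0.49 when it depended on T1 alike in both arms. It gave 0.39 to 0.40 when low-distress men left GET and high-distress men left ISP. The likelihood estimate was 0.49 to 0.50 throughout.
- Set B: 60 men per trial, 3,000 trials per scenario, baseline slope 0.6, residual SD 0.8, T1–T2 residual correlation 0.70, loss of about 20%. Completers-only gave 0.57 when distress drove loss in GET only. It gave 0.66 when high-distress men left GET and low-distress men left ISP. The likelihood estimate was 0.50 to 0.51.

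The two sets err in opposite directions because opposite loss patterns were assumed. Both made loss depend only on the observed T1 score (missing at random), which is the condition under which the likelihood estimate is expected to be right.

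**Step 4. What this does to planning.** Required sample size is proportional to 1/effect². Relative to a true 0.50:

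- planning on 0.66 gives (0.50/0.66)² = 0.57, about 43% too few;
- planning on 0.39 gives (0.50/0.39)² = 1.64, about 64% too many;
- planning on the averaged 0.35 gives (0.50/0.35)² = 2.04, about twice as many.

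For scale, the standard error of the contrast with 24 completers per arm and residual SD 0.8 is 0.8 × √(2/24) = 0.23. The set B biases of 0.07 to 0.16 are about 0.3 to 0.7 of that.

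**The case against.** The section says neither that men with a missing visit are excluded nor that T1 and T2 are averaged. A reader might infer that it plans both. It does not: these are properties of one way of fitting the model and of one term in it. The model can be fitted by likelihood and a T2 contrast drawn from it. The mixed-model sentence could also mean one joint model with a separate trajectory per arm. Handling of missing data is commonly left to the analysis plan, and the core of the intention-to-treat statement, analysis by allocated arm, is respected by ANCOVA.

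Much of this stands, and it is why the point is conditional on the classical form. It does not remove the point. The section names repeated-measures ANCOVA for the comparison, and mixed-effects models separately with another described role. The text therefore does not suggest that they are the same model, and it ties neither to T2.

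Three further readings are tempting but unsupported.

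- That the bias would favour GET: its direction depends wholly on the assumed loss pattern.
- That the biomarker analysis is invalid: with one follow-up, a baseline-adjusted repeated-measures ANCOVA reduces to ordinary ANCOVA, so this is mostly terminology.
- That within-arm change will be read as a treatment effect, despite selection on a low goal-navigation score or high screening distress: no within-arm test is stated.

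**Conclusion.** The point holds in conditional form. Run classically, the method named for comparing arms conflicts with the commitment to analyse men whatever their dropout, and its default arm effect is not the T2 contrast hypothesised for distress and self-regulation.

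The size cannot be fixed from the protocol. The range of 0.39 to 0.66 SD for a true 0.50 rests on assumed loss of about 20% that depends on T1 differently by arm. It illustrates the problem and does not bound it. Under random loss, or loss that depends on T1 alike in both arms, the bias is negligible to small. The averaging distortion vanishes if the T1 and T2 effects are equal.

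Severity is moderate. This is an external pilot whose main conclusions concern whether and how to proceed, and the sampling error of its effect estimate exceeds the set B biases. It still merits correction, because the distress results are intended to inform future sample size and the better analysis is already planned.

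**What to change.** For the questionnaire outcomes, name the mixed model as the between-arm analysis. Fit one joint model with arm, time, arm-by-time and baseline score by time, using every observed follow-up score from randomised men. State that the reported estimate is GET minus ISP at T2 with a 95% CI. Keep repeated-measures ANCOVA, if at all, as a labelled completers-only sensitivity analysis. For the biomarkers, specify ordinary baseline-adjusted ANCOVA at their single follow-up.

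The cost is wording in the protocol and analysis plan; no visits, participants or data are added. There are two limits to acknowledge. The likelihood analysis assumes that scores are missing at random, and men with no follow-up score at all still contribute nothing to the contrast. The number of such men in each arm should therefore be reported beside the estimate.
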